#### Site selection

This study is designed to investigate the impact of different models of ESD operating over defined geographical regions of the East Midlands, West Midlands, East of England, and North of England (clinical network boundaries). This will allow an investigation of the consequences of a Midlands and East initiative to implement ESD beginning in 2012 [25] contrasted with a region (North of England) that has been slower to implement ESD based on SSNAP post-acute organisational audit data [9]. Sites within each of the four regions will be defined according to Clinical Commissioning Group (CCG) and local authority boundaries. All individual ESD teams within each site that participate in the SSNAP clinical audit will be included.

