#### ESD impact on patient length of hospital stay

A key benefit of ESD identified in the original randomised controlled trials was a reduction in length of hospital stay [6, 7]. Hence, we have also included this measure in our proposed analysis. Using our multilevel modelling framework and controlling for our covariates, this analysis will examine how patient length of hospital stay is influenced by the presence or absence of an ESD service on their care pathway.

Independent of the ESD team data, 2015–2016 hospital SSNAP data will be analysed to determine if patients from admitting hospitals that have ESD available as part of their care pathway differ in total length of inpatient stay from patients from admitting hospitals that do not, whilst controlling for confounding variables (e.g. patient level characteristics highlighted above). For this analysis, patients will be nested within admitting hospitals rather than ESD teams, and hence, different datasets will be used. Hospital characteristics of interest are type of hospital (e.g. as recorded by the SSNAP team) and a measure of delayed transfers of care from hospital, derived from the Adult Social Care Outcomes Framework (ASCOF), to account for influence of provision of social care [30]. The outcome variable for these analyses will be hospital length of stay at the patient level.

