An additional analysis using a difference-in-difference, i.e. before-and-after design, will then be conducted to further investigate the magnitude of ESD impact on patient length of hospital stay [31]. This will provide a comparative analysis to the previous cross-sectional approach whereby we compare that 2015–2016 time period with a previous time period (2013–2014) in terms of ESD prevalence and its impact on inpatient length of stay across the two time periods. Difference-in-difference analysis enables investigation of differences in length of hospital stay over time and comparison between sites that have implemented ESD with sites that have not. To do this, the analysis requires use of data collected before and after the implementation of ESD. In this study, implementation of ESD is measured in terms of ESD being offered as part of the patients’ care pathway, from their admitting hospital and across the two time periods. Furthermore, we will determine which admitting hospitals had ESD as part of their care pathway at each time period, using patient-level SSNAP data, which tracks patient journey from first inpatient admission to final discharge destination.

### Work package 2

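### With only two periods, the length-of-stay difference-in-difference cannot separate an ESD effect from unequal underlying trends; dating the same records by quarter would let that assumption be examined.

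*Protocol article*

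**What the plan says.** The relevant text is in the protocol article, Work package 1, under 'ESD impact on patient length of hospital stay'. After a cross-sectional comparison of hospitals with and without ESD, the article states: "An additional analysis using a difference-in-difference, i.e. before-and-after design, will then be conducted". Its purpose is to examine further how large the ESD effect on stay is, as a comparison for the cross-sectional result.

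The structure is given in four statements:

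- Time: "we compare that 2015–2016 time period with a previous time period (2013–2014) in terms of ESD prevalence". The effect of interest is "its impact on inpatient length of stay across the two time periods".
- Exposure: "we will determine which admitting hospitals had ESD as part of their care pathway at each time period".
- Contrast: "comparison between sites that have implemented ESD with sites that have not".
- Data and outcome: status is determined "using patient-level SSNAP data, which tracks patient journey from first inpatient admission to final discharge destination". For the preceding cross-sectional analysis the outcome is stay for each patient: "The outcome variable for these analyses will be hospital length of stay at the patient level".

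No time unit finer than the two periods is named. The adjustment variables listed for length of stay are patient case-mix, type of hospital and a measure of delayed transfers of care. None is a calendar-time term.

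Under 'Site selection' in the same work package, the article explains that regions covered by a Midlands and East initiative beginning in 2012 are contrasted with "a region (North of England) that has been slower to implement ESD".

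**The concern.** A difference-in-difference removes fixed differences between hospitals and any change over time that all hospitals share. It does not remove a change that differs between adopting and non-adopting hospitals for reasons other than ESD. The causal reading therefore rests on parallel trends: without ESD, stay would have changed by the same amount in both groups.

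With one earlier and one later period, the comparison contains nothing that bears on that assumption. Fitting the model to individual patients does not help while time enters only as earlier or later, because the interaction of period with adoption is still a single contrast.

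Hospitals were not randomised to ESD, and the regions were selected for their different pace of adoption. Regions that move at different speeds on one part of the stroke pathway could also differ in how fast stay is changing. That is a possibility the design leaves open, not something the article reports.

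At stake is the size of the ESD effect on stay, which the article calls a key benefit in the original trials. This analysis is the one that could guard against fixed confounding in the cross-sectional result.

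**Working it through.** The article gives no sample size, effect size, standard deviation or mean stay for this analysis, so there is no figure of its own to reproduce. The check is algebra plus an illustration on assumed inputs.

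**Step 1: distance between the periods.** The labels can be read in two ways.

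- Two calendar years each: midpoints (2013 + 2015)/2 = 2014.0 and (2015 + 2017)/2 = 2016.0. Gap 2.0 years.
- Twelve-month audit years, taken here as April to March: midpoints 2013.75 and 2015.75. Gap 2.0 years.

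The gap is the same on either reading.

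**Step 2: what the estimate contains.** Let *s_A* and *s_N* be the underlying yearly changes in mean stay in adopting and non-adopting hospitals, taken as linear. Let *g* = *s_A* − *s_N*, and let δ be the ESD effect in the later period.

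- Change in adopting hospitals: δ + 2*s_A*
- Change in non-adopting hospitals: 2*s_N*
- Difference: δ + 2(*s_A* − *s_N*) = δ + 2*g*

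Two period means per group give one contrast and two unknowns, δ and *g*. A change common to all hospitals cancels; only a differential one stays.

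**Step 3: size.** The trend differences are assumed, since the article gives none.

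| Trend difference, days per year (assumed) | Added to the ESD effect, days |
|---|---|
| 0.1 | 2 × 0.1 = 0.2 |
| 0.25 | 2 × 0.25 = 0.5 |
| 0.5 | 2 × 0.5 = 1.0 |

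If stay falls faster in adopting hospitals, ESD looks better than it is; if it falls more slowly, ESD looks worse.

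**Step 4: illustration with no true ESD effect.** Assumed: 30 adopting and 30 non-adopting hospitals, 16 quarters, 40 patients per hospital and quarter, patient standard deviation 18 days, adoption at the start of 2015, 2,000 runs. Negative *g* means stay falls faster in adopting hospitals.

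| *g*, days per year | Two-period estimate, mean | Significant at two-sided 5% | Pre-adoption slope test significant | Estimate with hospital-specific linear trends, mean |
|---|---|---|---|---|
| 0 | 0.00 | 6% | 5% | −0.01 |
| −0.25 | −0.50 | 28% | 9% | 0.02 |
| −0.5 | −1.00 | 78% | 21% | 0.01 |
| −1.0 | −2.00 | 100% | 60% | −0.01 |

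The standard error was about 0.37 day for the two-period estimate and about 0.75 day for the trend-adjusted one.

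**Step 5: what the illustration says about a remedy.** Trend adjustment removes the bias at about twice the standard error. Total error of the two-period estimate, √(bias² + 0.37²), is:

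- *g* of size 0.1: √(0.2² + 0.37²) = 0.42
- *g* of size 0.25: √(0.5² + 0.37²) = 0.62
- *g* of size 0.5: √(1.0² + 0.37²) = 1.07

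Against 0.75 for the trend-adjusted estimate, the plain estimate is more accurate for the first two and less accurate for the third. The trend-adjusted estimate therefore belongs beside the plain one, not in place of it. Nor can a pre-trend test decide whether to show it: at 0.5 day per year the test was significant in only 21% of runs.

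**The case against.** The strongest reply is that this is one paragraph of a journal article. It names the method, cites a methods source, names two periods and says how exposure is found. A trend check or a finer time term could well sit in a fuller plan that is not shown, and every difference-in-difference rests on parallel trends. That is fair as far as it goes, and the article's silence about a trend check is not the point here. What remains is the structure it does state: two periods, one ESD status per hospital in each, and an effect read across the two.

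A reader might infer more than the article supports:

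- *That stay was already falling faster in adopting hospitals.* Nothing says so. 'Site selection' describes different speeds of adopting ESD, not different trends in stay, and a contrast in adoption is what the method needs.
- *That hospitals adopted ESD in response to temporarily long stays, which then fell back.* The article offers no support. For the Midlands and East it refers to a regional initiative.
- *That patient records are averaged into block means and the rest thrown away.* The article sets out multilevel modelling and a patient-level outcome. What is fixed is the time contrast, not the averaging of records.
- *That four years, or 16 quarters, of dated records are in hand.* This holds only if the labels mean calendar years. Audit years would give about eight quarters with a one-year gap. Dates are implied by a length-of-stay outcome and a tracked patient journey, but are not stated.

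Two further replies stand and limit the weight of the point. The sizes are assumptions, with no mean stay in the article to set them against. And this is an additional analysis within a mixed-methods evaluation, alongside a cross-sectional one.

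**Conclusion.** The point holds as an unchecked assumption built into the stated design, not as a demonstrated bias. As described, the estimate is the ESD effect plus twice the yearly trend difference, and the two-period comparison cannot show whether that second part is zero. For assumed differences of 0.1, 0.25 and 0.5 day per year it is 0.2, 0.5 and 1.0 day. The factor of two holds on either reading of the period labels and rests on a linear differential trend.

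A second consequence of one status per period is that a hospital adopting partway through a period is classed the same way for all of it. Because the initiative began in 2012, some hospitals may also have had ESD throughout the data and so have no true before period.

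The change is worth making because the analysis is meant to inform how large the ESD effect is, and the patient-level source should allow a better look at the assumption at little cost. Confidence is moderate: the structure is clear from the text, while the existence and size of any trend difference are unknown.

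**What to change.** Keep the two-period estimate and add the following to the analysis description.

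1. State whether the period labels mean calendar years or 12-month audit years.
2. Analyse the same patient-level records by calendar quarter, with hospital effects, quarter effects and case-mix. This gives 16 quarters on the calendar-year reading, or about 8 with a gap on the audit-year reading.
3. Date each hospital's adoption by its first quarter with ESD patients. For hospitals that change status, always show the quarter-by-quarter estimates before and after adoption.
4. Leave hospitals with ESD from the start of the data out of the pre-adoption check, since they have no pre-period.
5. Report an estimate with hospital-specific linear trends as a sensitivity analysis in all cases. Do not make it depend on a significant pre-trend test, which has low power.
6. Describe the ESD magnitude as resting on parallel trends to the extent that these results leave the question open.

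Cost: analysis wording and some programming, on records of the kind the plan already uses, provided admission or discharge dates are in the extract. The trend-adjusted estimate will have a much wider interval, with about double the standard error in the illustration. On the audit-year reading there are few pre-adoption quarters, so the check will be weaker still.

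### ESD exposure in the length-of-stay analysis is set by admitting hospital and time window, so patients admitted before a launch inside a window count as exposed and the difference-in-difference estimate is expected to shrink

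*Protocol article*

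**What the plan says.** The section on ESD impact on patient length of hospital stay plans two analyses.

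- **Cross-sectional, 2015–2016.** It asks whether "patients from admitting hospitals that have ESD available as part of their care pathway differ in total length of inpatient stay" from patients of hospitals without ESD. Patients are nested within admitting hospitals.
- **Difference-in-difference.** In the protocol's words, "we compare that 2015–2016 time period with a previous time period (2013–2014) in terms of ESD prevalence". The section states that "the analysis requires use of data collected before and after the implementation of ESD".

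Exposure is then defined: "implementation of ESD is measured in terms of ESD being offered as part of the patients’ care pathway, from their admitting hospital", across the two periods. The next sentence says how it will be assigned: "we will determine which admitting hospitals had ESD as part of their care pathway at each time period". The source is patient-level audit data that follow each patient from first admission to final discharge destination.

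The article gives no ESD start date and does not use a patient's admission date to place the patient before or after launch. It also does not say whether each window is two calendar years or a single audit year.

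**The concern.** A before-and-after comparison has to separate patients admitted before the service existed from those admitted after. One status per hospital per window does this only if launches fall outside the windows. When a launch falls inside, the label puts both kinds of patient in the same group.

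This matters most for the difference-in-difference, because the hospitals that change status identify the effect, and they are the ones with a launch date near or inside the data. The section's stated purpose is to gauge the magnitude of the ESD effect on stay, and the study asks whether trial benefits are realised in practice. A diluted estimate could be read as routine services falling short of the trials when part of the shortfall comes from exposure coding.

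**Working it through.** The plan states no effect size, power, sample size or launch dates for this analysis, so there is no figure to reproduce. The check is dilution algebra, and every launch time below is an assumption.

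**1. A single hospital that switches status.** Take a window of W months, uniform admissions, a launch m months in, and patients admitted before launch treated as unexposed. The share of labelled patients who had access, which is also the share of the effect kept, is (W − m)/W.

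| Window W | Launch month m | Share kept |
|---|---|---|
| 24 | 0 (at the start) | 1.00 |
| 24 | 6 | 18/24 = 0.75 |
| 24 | 12 | 12/24 = 0.50 |
| 12 | 6 | 6/12 = 0.50 |

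A launch before the first window, or in a gap between windows, loses nothing.

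**2. The comparators.** Let a2 and b1 be the true access shares of switching hospitals in the late and early windows, and c2 and c1 those of the comparators. With hospital and period effects, the share of the true effect kept is

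(a2 − b1) − (c2 − c1).

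A hospital launching at month 12 of 2013–2014 and labelled ESD in both windows has c1 = 0.50 and c2 = 1.00, so its access rises by 0.50 while its label does not move. Suppose switching hospitals launch at month 6 of the late window (a2 = 0.75, b1 = 0) and a fraction p of comparators, weighted by patients, is of this kind:

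- p = 0: 0.75 − 0 = 0.75
- p = 0.25: 0.75 − 0.25 × 0.50 = 0.625
- p = 0.50: 0.75 − 0.50 × 0.50 = 0.50

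**3. The cross-sectional estimate.** Hospitals labelled ESD in 2015–2016 include services already running before the window, which lose nothing. If a fraction q of labelled patients comes from hospitals that launched inside the window, with mean share kept r, the overall share is 1 − q(1 − r). With q = 0.20 and r = 0.50 this is 1 − 0.20 × 0.50 = 0.90, a smaller loss than in the difference-in-difference.

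**4. Consequence for precision.** The sample needed to detect the diluted effect scales as 1/share². A share of 0.75 needs 1/0.5625 = 1.78 times the patients, and 0.50 needs 1/0.25 = 4 times. A two-sided 5% test with 80% power at full access would have power Φ(0.75 × 2.80 − 1.96) = Φ(0.14) = 56% at 0.75, and Φ(0.50 × 2.80 − 1.96) = Φ(−0.56) = 29% at 0.50.

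**5. Dependence on the windows.** If 2013–2014 and 2015–2016 are calendar years, they touch, and a hospital going from no ESD to ESD must have launched during the later window or exactly at its start. If they are single audit years, there is a 12-month gap. Launches in the gap are coded correctly, and only launches inside a window are affected.

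**6. Dependence on the labelling rule.** The above takes a hospital to have ESD in a window if it had it at any time in that window. If ESD throughout were required instead, patients admitted after a launch inside a window would be counted as unexposed, which also tends to shrink the contrast.

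**The case against.** The strongest defence is that availability at the admitting hospital is a legitimate service-level effect, similar to intention to treat. It avoids selecting patients by eligibility for ESD or receipt of it. That stands, and the repair should keep it. But availability has a date, and patients admitted before launch had no service available under any definition. The section also words its question as "how patient length of hospital stay is influenced by the presence or absence of an ESD service on their care pathway", which points to each patient's own pathway.

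A second objection is that a condensed article need not give every coding rule. That is true of thresholds, but here the article does state the unit and time resolution of exposure.

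Several stronger readings are tempting and should not be drawn:

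- **Every hospital that starts ESD does so inside a window.** The WP1 site selection section dates the Midlands and East initiative from 2012, before both windows. Services that launched then are unaffected.
- **Transferred patients are mislabelled.** The label concerns the admitting hospital's pathway, and the data follow patients through to final discharge.
- **A handful of ESD discharges makes a hospital exposed.** The article states no cut-off, but its silence is not a rule that none applies.
- **Hospitals serve areas with and without ESD.** The protocol says that "Sites within each of the four regions will be defined according to Clinical Commissioning Group (CCG) and local authority boundaries". This defines study sites and does not show mixed access within one hospital.
- **A loss in days.** Any such figure needs an assumed true effect that the document does not give.
- **Bias is always toward no effect.** It is the expected direction, but comparators that lost access would push the other way. For example, a2 = 0.80, b1 = 0, c1 = 0.50 and c2 = 0.20 gives 0.80 + 0.30 = 1.10.

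**Conclusion.** The point holds for launches inside a window. The stated hospital-by-period label counts patients admitted before such a launch as exposed, although the section itself requires data from before and after implementation. The expected result is an attenuated difference-in-difference estimate and, to a lesser extent, an attenuated 2015–2016 cross-sectional estimate.

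The size is unknown. It depends on launch months, on how many hospitals launched inside each window, and on whether the windows are contiguous. Under the illustrative inputs the share of the effect kept runs from 0.75 down to 0.50. It is 1.00 if all launches fell before, between or exactly at the start of windows. This should be changed before analysis, since the data source the protocol already names appears sufficient, but it does not invalidate the design.

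**What to change.** 1. Use the patient journeys to derive each admitting hospital's ESD start month, defined as the first month of sustained ESD discharges.
2. Code ESD availability, not receipt, by the patient's admission date relative to that month. Exclude a short run-in around launch, since patients admitted just before it may still be in hospital when the service opens. Replace the single period term with calendar-time terms fine enough to match.
3. State whether each window is two calendar years or one audit year.
4. If the data show only partial ESD coverage at a hospital, use its monthly share of discharges with ESD as a sensitivity analysis, or the patient's area of residence if that is held (the article does not say). Do not set exposure by discharging hospital: that is determined after admission and may be related to severity and stay.
5. Keep the hospital-by-period label as a further sensitivity analysis, so that the effect of the coding is visible.

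The cost is mainly derivation work on the audit journeys. The drawback is that a threshold for sustained ESD discharges must be chosen. It should be fixed in advance and varied in one sensitivity analysis.

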#### Site selection

Using a purposive sampling approach, case study sites from work package 1 will be selected based on the level to which evidence-based ESD has been implemented (contrasting ESD models) and the influence of rurality on ESD effectiveness (urban vs. rural sites).

#### Recruitment and interviews

##### Staff interviews

Semi-structured one-to-one interviews will be conducted with up to eight NHS staff informants at senior management, service lead, and commissioning level at each ESD site. Stakeholders (e.g. commissioners, ESD team leads) will be identified through collaboration with the national audit team and stroke clinical leads operating in each region. We will also liaise with NHS senior staff, invited to be part of our steering group panel, to ensure we identify and engage stakeholders effectively. Semi-structured interviews will allow us to explore individual stakeholder perceptions on a one-to-one basis, using a topic guide and prompts informed by our programme theories. These ‘realist’ interviews will be designed to expose individual stakeholder perspectives on the mechanisms involved in the implementation, delivery, and effectiveness of ESD and how these relate to contextual factors and desired outcomes.

